#### Interim analysis

The Data Safety Monitoring Board (DSMB), comprising a biostatistician and two clinician-investigators completely independent of the sponsor and funders, will oversee a single interim analysis of the study data halfway through enrolment (i.e. after 100 participants have been enrolled). Rates of early clinical failure (the primary outcome) will be calculated for each arm of the study and the study will be prematurely terminated if the proportion of treatment failures in the experimental arm is statistically significantly greater (*p* < 0.0001) than 7.5% *more* than the proportion of treatment failures in the control arm. Should one of the arms of the trial be found to be this much greater than the other, the DSMB will order unblinding, and should the increased failure rate be in the control arm, the trial will continue, as this would certainly be due to chance. The trial will not be stopped early for benefit simply because trials stopped early for benefit have been shown to consistently overestimate treatment effects [18], and, if short-course therapy is truly non-inferior to standard therapy, participants in the trial would be at overall decreased risk compared with non-participants due to the surveillance measures built into the trial. Additionally, the DSMB will review safety data on a biannual basis for each arm of the study; specific items that will be monitored include the number of participants in each arm that clinically worsen on or after 6-days post recruitment and require a change in antimicrobial therapy; the number of participants in each arm that develop an SAE; and the number of participants in each arm that clinically worsen after the primary outcome measurement and require institution of antimicrobial therapy. If safety concerns arise, more frequent meetings will be initiated, and the trial may be terminated. The DSMB will receive immediate notification and reports of serious adverse reactions related to study procedures or medications.

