### Statistical analysis

#### Sample size

We estimate the baseline failure rate of standard therapy to be ~ 5%; this estimate is consistent with previous studies in children [13], is less than in similar adult studies [7], and is the approximate rate that was seen in the pilot study. We will use a non-inferiority margin of an additional 7.5%. As this is a non-inferiority trial, the crucial statistical comparison will be between the 97.5% (one-sided) CI of the difference between the failure rate of the experimental arm and the standard therapy arm; should the upper bound of this difference be smaller than 7.5%, a conclusion of non-inferiority will be reached. As the maximum baseline failure rate in the reference arm is probably 5%, the maximum failure rate in the experimental arm that would still be felt to be “non-inferior” would be 12.5%; the margin of 7.5% was selected to make the maximum failure rate in the experimental arm less than 13.5%, the median acceptable failure rate in the treatment of CAP identified in a survey of infectious-disease physicians [37]. Setting α at 5%, with 80% power, 135 participants in each arm will be required for this trial (PASS software package, NCSS LLC, Kayesville, UT, USA); as we will have accrued ~ 60 subjects in the pilot to be “rolled over”, an additional 210 participants will be required. Our experience conducting the pilot, combined with an analysis of visits to the EDs of the study sites, leads us to believe that this target should be achievable. It is estimated that the target sample size should be attainable after 2 years of enrolment.

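### The interim harm rule, p < 0.0001 against an excess of 7.5 points, would rarely fire even if the 5-day arm failed four to six times as often as control

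*Protocol article*

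**What the plan says.** The Interim analysis section of the protocol article states that the DSMB "will oversee a single interim analysis of the study data", timed "halfway through enrolment (i.e. after 100 participants have been enrolled". The stopping criterion is that "the study will be prematurely terminated if the proportion of treatment failures in the experimental arm is statistically significantly greater", and the comparison is completed by "p* < 0.0001) than 7.5% *more* than the proportion of treatment failures in the control arm". The null value is therefore an excess of 7.5 points, not zero. Neither the test nor its sidedness is named.

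The same section rules out stopping for benefit. It also has the DSMB review safety data by arm twice a year: worsening from day 6 with a change of antimicrobial, SAEs, and worsening after the primary visit. The trial may be ended on safety grounds. No numeric threshold is attached to that review.

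The Sample size section supplies the yardsticks. Control failure is taken as about 5% and the margin as 7.5 points, and "the maximum failure rate in the experimental arm that would still be felt to be “non-inferior” would be 12.5" per cent. The margin was chosen to stay below "13.5%, the median acceptable failure rate in the treatment of CAP identified in a survey of infectious-disease physicians".

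**The concern.** The rule stacks two barriers to stopping: a null moved up by the whole non-inferiority margin, and a p-value of the kind normally used to protect the final alpha from early success claims. At an early look with few expected failures, the combination may leave the rule unable to respond to failure rates well above those the protocol itself treats as acceptable.

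If so, children would go on being randomised to an arm failing at 20-30% against 5%, in a trial that could no longer reach its intended conclusion. The DSMB would have only its unquantified safety review to act on.

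**Working it through.** **Inputs.** Control failure 5%, margin 7.5 points and 135 per arm (Sample size); one-sided alpha 0.025 and power 80% (Abstract, Methods); look after 100 enrolled, p < 0.0001 (Interim analysis). Assumed: an even split of 50 per arm, with all children evaluable.

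**The plan's own figure.** n per arm = (1.960 + 0.842)² × 2 × 0.05 × 0.95 / 0.075² = 132.6, so 133, close to the stated 135. The 5% and 7.5-point inputs are therefore the right ones to carry forward. The document gives no operating characteristics for the interim rule.

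**Where the rule first fires.** z = (p5 − p10 − 0.075) / SE, with unpooled SE = √[p5(1 − p5)/50 + p10(1 − p10)/50]. The cut-off is 3.719 one-sided and 3.891 two-sided. With 3/50 control failures:

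- 22/50: (0.44 − 0.06 − 0.075) / √(0.004928 + 0.001128) = 0.305 / 0.0778 = 3.92, stop.
- 21/50: (0.42 − 0.06 − 0.075) / √(0.004872 + 0.001128) = 0.285 / 0.0775 = 3.68, continue.

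The Farrington-Manning score statistic at 22 against 3 is 3.62, so that test needs 23. At a true 25% one expects 0.25 × 50 = 12.5 failures in the 5-day arm.

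**Probability of stopping.** Exact sum over two independent binomials, control 5%, one-sided; each range covers the score and Wald tests:

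| True 5-day failure | Protocol rule, 50 per arm | Protocol rule, about 80 per arm | Zero excess, one-sided p < 0.001, 50 per arm |
|---|---|---|---|
| 20% | 0.2-0.3% | about 0.8% | 16-20% |
| 25% | 1.5-2.3% | 6-7% | 36-43% |
| 30% | 7-10% | 22-26% | 60-66% |

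The 80-per-arm column is (100 + 60) / 2, which applies if the rolled-over pilot children are added to the 100. Reading the p-value as two-sided, or using a pooled variance, lowers the protocol-rule figures (down to 0.3% at 25% with 50 per arm). With 67 per arm, half of 270, the figure at 25% is 0.9-4.7% across tests.

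**A looser reading of the rule.** If it meant an observed excess above 7.5 points together with p < 0.0001 against zero, it would need 17-20 failures against 3 and would stop 8-20% of the time at 25%.

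**What continuing preserves.** At 135 per arm, the chance that the final analysis shows non-inferiority is about 0.008% at a true 20% against 5%, and below 0.0001% at 25%.

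**Cost of the example boundary (zero excess, one-sided p < 0.001).** With 3 control failures it first fires at 15: Wald z = 0.24 / √(0.0042 + 0.001128) = 3.29 against a cut-off of 3.09. Under equal 5% rates it stops about 0.006% of the time. A trial halted exactly on the boundary gives up little: even if every later child in both arms failed at 5%, the chance of finishing non-inferior would be at most 0.7% (9 against 0), 0.02% (12 against 1) and under 0.01% from 14 against 2.

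**The case against.** **The margin is the protocol's own definition of unacceptable excess, and a strict interim level is a recognised choice.** Both are true, and nothing here contradicts another part of the document. But a strict level usually protects the final alpha. This trial cannot stop for benefit, and stopping for harm can only reduce the chance of wrongly declaring non-inferiority. The section explains why it will not stop for benefit; it gives no reason for the strictness on harm.

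**A reader might infer that this is the only protection.** It is not. The review by arm can end the trial, and it tracks worsening from day 6 onward, the period in which the arms differ. Calls at days 3-5 and 7-10, urged re-evaluation and unblinding protect individual children. What stands is narrower: this is the only numeric harm rule in the document. A DSMB charter, not shown, may hold others.

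**A reader might also infer that the rule fails at any multiple of the control rate.** Twice control is 10%, which the Sample size section still counts as non-inferior; the trial would then keep about a 10-14% chance of success. The case begins at about 20%.

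**The size of the look is uncertain.** The stated 100 is close to half of the 210 new children and short of half of 270, so the pilot children may or may not be in it. Counting them raises the stopping probabilities but leaves the rule insensitive at 20-25%. Conversely, because the outcome is read at day 14-21, fewer than 100 may be evaluable if the look is taken when the 100th child enrols, which lowers them.

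**The replacement also misses most cases at 20-25% with 50 per arm.** That stands: a single early look limits detection whatever the boundary.

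**Conclusion.** The point holds as a design weakness that is cheap to correct. At 20-30% true failure against 5%, the protocol's rule stops in at most about one trial in ten with 50 per arm, and about one in four with 80 per arm. At those rates the final chance of success is below 0.01%, so continuing does not protect the trial's question. Type I error control does not explain the strictness.

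The figures rest on a 5% control rate, equal arms, full evaluability and the literal reading of a null shifted by 7.5 points. The looser reading softens the result (8-20% at 25%) without reversing it. The documents do not support saying that children are otherwise unprotected, or that the rule is at fault for failure rates inside the margin.

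**What to change.** Restate the interim harm boundary as 5-day failure exceeding 10-day failure, with a null of zero excess, at a less extreme level and with a named score or exact test. One-sided p < 0.001 is offered as an example only, since the documents do not fix a value. State whether the rolled-over pilot children count towards the 100, and give the stopping probabilities at the actual evaluable size. Keep the rule against stopping for benefit; no alpha adjustment is then needed.

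The change is to wording in the protocol and any DSMB charter, with no added participants. The downside of the example boundary is a false stop under equal 5% rates of about 0.006% at 50 per arm, and up to about 0.04% at 80. If the true 5-day rate were 10%, inside the margin, it would stop about 0.5-0.7% of the time at 50 per arm and about 2% at 80.

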### Study monitoring

On-site monitoring of the MCH site and the CHEO site, both tertiary-care children’s hospitals, will be conducted by qualified research personnel (the main study PI, the main study research coordinator, or quality assurance personnel) as required. Monitoring will be conducted through personal visits with the local PI and site staff (every 3–6 months or as needed based on enrolment and participant study visits) as well as any appropriate communications by mail, fax, e-mail, or telephone. The purpose of monitoring is to ensure compliance with the protocol and the quality and integrity of the data. The essential documents in the investigator regulatory files will be monitored and checked for accuracy and completeness. The monitor will identify any items missing from the regulatory binder. Site personnel are responsible for maintenance of the regulatory binder. The consent document will be reviewed for content to ensure it contains the required (and additional, as applicable) regulatory elements. The consent document will be compared to the protocol and site-specific REB procedures for informed consent documentation to ensure agreement between the two documents. Consent form monitoring will be documented in the monitoring time point report.

#### Knowledge translation (KT) plan

The nature of the proposed trial is strongly toward the pragmatic end of the clinical trial spectrum [43]; consequently, the results of the trial will be positioned for rapid integration into clinical practice by Canadian physicians. Research team members will collaborate with established networks of clinicians experienced in the dissemination of clinical guidelines to healthcare practitioners, i.e. the Canadian Paediatric Society, Association of Medical Microbiology and Infectious Disease Canada, Infectious Disease Society of America, Canadian Association of Emergency Physicians, and Pediatric Emergency Research Canada (PERC). Given that PERC, a highly successful research network involving 15 children’s hospitals, represents a key group of knowledge users for this study, the executive was invited to the table in the design phase to ensure that the study objectives were relevant to Canadian emergency physicians and the study protocol was structured in such a way to optimize both internal and external validity. PERC has since unanimously endorsed the proposed study as one deserving of its support. The above-noted collaborations will be stimulated though presentation at major Canadian and American meetings (Pediatric Academic Societies, Canadian Paediatric Society, etc.); healthcare decision makers will be provided a one-page synopsis of the results and invited to meet with study team members to discuss the implications. The end-of-grant KT strategy will also focus on publication of results in a peer-reviewed open-source journal (preferably a general paediatric journal because of the broad audience), oral and poster presentation at local and national meetings, and leveraging dissemination through the diverse professional networks of the research team members (the applicant and co-investigators are trained in disciplines including paediatric infectious disease, adult infectious disease, medical microbiology, clinical epidemiology, and paediatric emergency medicine). In all cases, messages will be tailored to ensure relevance to the target audience.

## Discussion

SAFER is a pragmatic randomized controlled trial designed to embrace the conditions of real-world emergency medicine practice and “bridge the gap”’ between research and care. The pragmatic nature of our study will ideally position the results for rapid integration into clinical practice by Canadian physicians.

As is the case for any randomized controlled trial (RCT), there are aspects to its design which are not optimal. One issue is that should children without bacterial pneumonia be included, statistical “noise” would be introduced, which might mask a true “signal” indicating that 5 days was in fact inferior to 10 days of high-dose amoxicillin (type I error). Unfortunately, there are no consensus criteria (clinical, radiologic, or otherwise) for the diagnosis of pneumonia, and so all CAP trials must construct a definition that appears “appropriate”. Our definition is almost identical to the “reference standard” in a recent study designed to investigate the accuracy of ICD-9-CM billing codes [44] and very similar to those used in other clinical trials [45–47] (many studies of pneumonia simply use clinician diagnosis as a definition [48–50], which is often imprecise and subjective). The inclusion of fever as a necessary criterion will diminish the probability of recruiting participants with pertussis, which is much less likely to be associated with fever [51], or non-infectious conditions. The necessity for participants to display a respiratory symptom or sign will diminish the probability of recruiting those with infections of other organ systems who are erroneously diagnosed with pneumonia. The requirement for participants to have a chest radiograph displaying a pneumonic infiltrate will likely increase the probability that they have an infection caused by a bacterial pathogen. Finally, since the aim of this pragmatic trial is to answer a real-world question asked by emergency physicians, it is important that all study participants are actually diagnosed with CAP. Unfortunately, none of the above is sufficient to reliably distinguish viral from bacterial pneumonia. It is very difficult to reliably determine the microbiologic aetiology of paediatric CAP without percutaneous lung biopsy, which has been applied in some settings [52], but is not practical in North America. Gram staining/culturing of sputum can help identify the aetiology of adult CAP but the difficulty of obtaining an adequate sputum sample from a young child renders it effectively useless in the paediatric ED. Culture or PCR of nasopharyngeal swabs (NPS) can readily detect *S. pneumoniae*, but its detection has not yet been shown to be specific for the diagnosis of pneumonia, as colonization was previously found to be common in young children [25]. Furthermore, preschoolers commonly develop viral pneumonia [5]. A recent, large multicentre prospective cohort study demonstrated that 73% of children admitted to hospital with severe pneumonia in the USA in 2010–12 had a detectable respiratory viral pathogen, compared to only 15% in whom a bacterial pathogen could be found [53]. Many centres routinely use multiplexed PCR panels that can detect almost all common important respiratory viruses in NPSs with high sensitivity and specificity [54]. However, it should be emphasized that the detection of a respiratory virus in an NPS does not rule out bacterial co-infection, a phenomenon that appears to be relatively common [55]. Given the extreme difficulty in discerning between viral infection and viral and bacterial co-infection, it should not be surprising that radiographic criteria for distinguishing between viral and bacterial pneumonia have never been developed, though many clinicians would presume that a child who had an alveolar infiltrate on chest radiograph would have a bacterial pulmonary infection. Other investigators have used CRP or white blood cell (WBC) count cutoffs to minimize the probability of recruiting patients without bacterial pneumonia; however, not only is there substantial overlap between the CRP/WBC distributions in children with viral and bacterial pneumonia, but in many regions blood work is rarely requested for children without severe pneumonia. Consequently, insistence on this testing would bring about unnecessary inconvenience and pain for participants and their families; furthermore, an algorithm that required blood work to stratify the severity of CAP would limit the usefulness of this testing in a real-world scenario. The SAFER trial is attempting to provide high-quality evidence for the management of children encountered on an everyday basis by clinicians working in North American EDs, and so inclusion of some children who may not have bacterial disease will not limit the generalizability of the results of the study.

The selection of the non-inferiority margin has a significant impact on trial outcome. It is clear that clinical considerations should inform the determination of the margin; if the margin is judged as unacceptably wide to clinicians, a “positive” non-inferiority trial will have little impact on practice. However, selection of the margin based solely on the clinical experience of the principal investigator should probably be avoided, despite how common this has been in the past. The US Food and Drug Administration (FDA) has provided guidance relating to statistical considerations affecting the selection of the non-inferiority margin [39]; note that their main concern seems to be that if the experimental treatment is found to be non-inferior to the standard therapy, there is sufficient evidence to be reasonably confident the experimental treatment is also superior to placebo [39]. The FDA draft guideline first instructs investigators to review meta-analyses of clinical trials of the standard therapy compared to placebo to discern the pooled estimate of efficacy; if only single trials are available, they can be used, but there will be much lower precision in the estimates of efficacy. Unfortunately, we cannot follow this guidance for the statistical determination of an appropriate margin for a trial such as SAFER because we do not have reliable data about the failure rate of placebo treatment of bacterial pneumonia in children living in the modern era. Estimates of child CAP-specific mortality from the pre-antibiotic era cannot be used since this would without doubt overestimate CAP-specific mortality in children today.

Adherence to medication is, in general, difficult to ensure. Caregivers of participants in this trial will be reminded far more frequently of the need to administer medication (via RA reminders and study diaries) than they would otherwise be; our adherence measures are similar to those in other major recent RCTs comparing short-course and standard-course antimicrobial therapy in children [56]. Despite this, it is entirely possible that adherence will be suboptimal, which could also predispose to a false conclusion of non-inferiority, especially if adherence to medication drops off after 5 days. From a practical standpoint, this is still important information for clinicians managing real patients, and would not greatly affect the generalizability of the results of the study (Additional file 1).

### Trial status

Actively recruiting since August 2016 using protocol v5.0 (date 12 August 2016).

## Abbreviations

ARO: Antibiotic-resistant organism
CAP: Community-acquired pneumonia
CHEO: Children’s Hospital of Eastern Ontario
CRP: C-reactive protein
DSMB: Data Safety Monitoring Board
ED: Emergency Department
FDA: Food and Drug Administration
HIV: Human immunodeficiency virus
IDSA: Infectious Disease Society of America
ITT: Intention-to-treat
MCH: McMaster Children’s Hospital
NPS: Nasopharyngeal swab
PERC: Pediatric Emergency Research Canada
PI: Principal Investigator
RA: Research Assistant
RCT: Randomized controlled trial
REB: Research Ethics Board
WBC: White blood cell
